### Sample Size

It is expected that, under conditions of usual care, the rate of medication-related hospital readmissions within 30 days among patients discharged following an AMI is 7% [40]. Interventions have reduced this rate from 7% to 4.9% (an absolute risk reduction of 2.1%) [41]. As mentioned previously, only a subset of the population (those identified as being at highest-risk based on model scoring and/or clinician referral) will be targeted to receive the intervention. Guided by previous studies and resources, we expect to prioritize the top 25% of patients at high-risk of medication-related readmission [42]. An additional 10% of patients are expected to be referred by the treating team. However, the final proportion of patients who will be triaged for intervention will be guided by a local audit following the development of the risk model. Because the high-risk patients will likely have a higher rate of potential readmission (ie, >7%), we expect that an intervention applied to only this group will still produce an absolute risk reduction of at least 2.1% averaged across the entire intervention sample, even though we expect the risk in the low-risk group to remain unchanged. Therefore, the sample size calculation is based on the overall sample required, not just the high-risk group.

Assuming a baseline risk of readmission of 7% and a significance level of .05, a sample size of 1990 participants is required in both the prestudy and intervention periods (ie, a total of 3980 patients across both prestudy and intervention periods) to detect an absolute risk difference of 2.1% with a power of 0.80. We assume a minimal dropout and refusal rate of 10%; taking this into account, we aim to recruit 2211 participants into each 12-month period (a total of 4422 participants across both the prestudy and intervention periods). We expect 35% of patients (~775 patients) to be flagged as high risk, consent to the study, and be given the TOC intervention. The remainder of the patients enrolled in the study will be given usual care as described earlier. Delivering the TOC service to 775 participants across the study sites over 12 months is both logistically feasible and achievable.

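### The 80% power rests on a 2.1-point drop averaged over the whole post cohort, which about 35% treated can deliver at the implied 30% relative effect only if every event falls among them

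*Protocol article*

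**What the plan says.** All the inputs stand in the Sample Size section of the protocol article.

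- Baseline and significance level: "Assuming a baseline risk of readmission of 7% and a significance level of .05".
- Source of the effect: "Interventions have reduced this rate from 7% to 4.9% (an absolute risk reduction of 2.1" points).
- Target: 1990 patients per period "to detect an absolute risk difference of 2.1% with a power of 0.80".
- Who is treated: "We expect 35% of patients (~775 patients) to be flagged as high risk, consent to the study, and be given the TOC intervention". This is made up of the top 25% by model score plus 10% referred by the treating team. The final proportion is left to a local audit.
- Who is not affected: "even though we expect the risk in the low-risk group to remain unchanged".
- The bridging assumption: "intervention applied to only this group will still produce an absolute risk reduction of at least 2.1% averaged across the entire intervention sample". The reason given is that high-risk patients probably have a rate above 7%.
- Inflation: "We assume a minimal dropout and refusal rate of 10%; taking this into account, we aim to recruit 2211 participants into each 12-month period".

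The Statistical Analysis section makes the whole pre cohort against the whole post cohort the primary comparison, by logistic regression with a study-period term. The untreated 65% of the post cohort are therefore in the primary contrast.

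**The concern.** The section takes an absolute reduction reported for interventions elsewhere and assigns the same reduction to a cohort in which about two thirds receive nothing new. It sees that this dilutes the effect, and argues that the higher risk of the treated patients makes up for it. It does not say how much higher that risk must be, what share of all events it expects among treated patients, or what relative effect it assumes there. Without those figures, 2.1 points cannot be called a floor.

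At stake is the meaning of the main result. If the true average drop is well below 2.1 points, a worthwhile service could easily give a non-significant primary comparison. The Limitations section names under-recruitment as the threat to power, so a reader would not look for this cause.

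**Working it through.** **Inputs from the Sample Size section.** Usual-care risk 7%; cited post-intervention risk 4.9%; alpha .05 (sidedness not stated; two-sided reproduces the plan's figure); power 0.80; 1990 or 2211 per period; 35% treated; zero effect in the rest. The 30% relative reduction is derived, 2.1/7 = 0.30; the document does not print it.

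**Input not in the documents.** The share *s* of usual-care events that fall in the treated 35%. It is varied below as an assumption.

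**Step 1: reproduce the plan.** For two proportions, 7% against 4.9%, two-sided 0.05 and 80% power, the pooled-variance formula gives 1991 per period and the unpooled one 1988. The plan states 1990. Power at 1990 is 80.0%. Inflation: 1990/0.9 = 2211. Treated: 0.35 × 2211 = 774, stated as about 775. The arithmetic is sound. With all 2211 analysed and a 2.1-point drop, power would be 84%.

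**Step 2: the drop needed in treated patients.** With no effect in the other 65%, average drop = 0.35 × drop in the treated. So the treated need 2.1/0.35 = 6.0 points.

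**Step 3: the relative reduction this implies.** Treated risk = 7% × *s*/0.35, and required relative reduction = 6.0 / treated risk.

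**Step 4: power at a 30% relative effect in the treated.** Average drop = 7% × *s* × 0.30, and post-cohort risk = 7% minus that drop. For example, *s* = 70% gives a drop of 1.47 points and a post risk of 5.53%. Power uses the same two-proportion test as step 1.

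| Share *s* of events in treated 35% | Treated risk | Relative reduction needed for 2.1 points | Average drop at 30% relative effect | Power, 1990 per period | Power, 2211 per period |
|---|---|---|---|---|---|
| 35% (no enrichment) | 7% | 86% | 0.74 points | 15% | 16% |
| 50% | 10% | 60% | 1.05 | 27% | 29% |
| 60% | 12% | 50% | 1.26 | 37% | 40% |
| 70% | 14% | 43% | 1.47 | 48% | 52% |
| 80% | 16% | 37.5% | 1.68 | 60% | 64% |
| 100% | 20% | 30% | 2.10 | 80% | 84% |

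In the last row 0.35 × 20% = 7%, so the treated group supplies every event and the other 65% have none. At a 30% relative effect, 2.1 points is therefore the ceiling, and power at 1990 is below 80% for any share under 100%.

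**Step 5: what 80% power needs at 2211.** Solving for the average drop gives 2.0 points, or 2.0/0.35 = 5.7 points in the treated. As a relative reduction this is 2.0/(7 × 0.70) = 41% at *s* = 70% and 2.0/(7 × 0.60) = 48% at *s* = 60%.

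**Step 6: refusal, if flagged patients who decline remain in the post cohort.** Suppose 2.1 points would hold at full uptake. With 10% declining, the average drop is 0.9 × 2.1 = 1.89 points, and power at 2211 is about 75%.

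**The case against.** Every printed figure reproduces, and the section discusses dilution openly. This is an optimistic assumption and not a calculation error. That stands, and the point is framed accordingly.

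The 30% relative effect is inferred. The section does not say whether everyone was treated in the cited work or whether its patients were selected for risk. Carrying over a relative effect is itself an assumption. That also stands, and it is why the relative effect should be varied. It does not rescue the claim, because a 6.0-point drop in the treated is needed on any scale, and a risk merely above 7% does not establish it.

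A reader might go further and conclude that the trial has about 40–52% power. The documents do not support that as a single figure. It needs 60–70% of events in the treated group and all 2211 per period analysed; at 1990, to which the stated 80% belongs, the same shares give 37–48%. No event share, discrimination figure or high-risk event rate is printed.

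A reader might also infer that the 10% refusal allowance is simply wrong. The 35% is described as already consenting and treated, and the intention-to-treat wording covers non-completers, withdrawals and deaths, without saying what happens to a flagged patient who declines the offer. A consent waiver covers usual-care patients, so such patients could stay in the cohort, but this is not stated. The dilution in step 6 is conditional on that reading.

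Finally, it is tempting to promote a pre-post comparison of model-flagged patients to key secondary analysis because it is less diluted. The risk model was planned on patients at two of the three sites from July 2023 to June 2024, the same months as the precohort. Flagged precohort patients may look riskier partly because the model was fitted to them, and post risk could then fall with no treatment effect. High-risk subanalyses are already planned, and this point gives no ground to elevate one.

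**Conclusion.** The concern holds as a fault in the effect assumption. The plan's inputs do not support an average drop of 2.1 points or more: this requires 6.0 points in treated patients, a relative reduction of 60% down to 37.5% as the event share rises from 50% to 80%. At the 30% relative reduction implied by the cited 7% to 4.9%, the stated 80% power at 1990 per period is reached only when no event occurs outside the treated 35%.

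The shortfall depends on the assumed event share: roughly 27–60% power at 1990 and 29–64% at 2211 for shares of 50–80%. These figures also rest on a 30% relative effect in the treated, no effect in the rest, exactly 35% treated, and an unadjusted two-sided comparison of two proportions.

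**What to change.** 1. Withdraw the claim that the averaged reduction will be 2.1 points or more. Replace it with a power table over an explicit range of event share and relative effect, at both 1990 and 2211. State that 80% power at 2211 needs about 2.0 points averaged, 5.7 points in the treated, or about 41–48% relative for event shares of 70–60%.
2. Take the event share from the risk tool, which the Results section reports as developed and in use. Use its cross-validated sensitivity at the chosen cut-off. Apparent sensitivity may be optimistic because of the overlap with the precohort period. Add an allowance for clinician referrals, which the model's sensitivity does not cover. No post-period outcome data are needed.
3. State whether flagged patients who decline remain in the post cohort. If they do, show refusal as effect dilution as well as lost sample.
4. Name dilution beside under-recruitment in the Limitations section as a reason why power may fall short.

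The cost is wording and a short calculation, with a less favourable power statement. Enrolment and the primary comparison do not change.

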### Precohort

All patients admitted to the study sites with an index admission for AMI or CS between July 1, 2023, and June 30, 2024, will be included. A waiver of consent has been granted to collect these retrospective data for the historical usual care control group.

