### Eligibility Criteria

The inclusion criteria are as follows:

Aged ≥18 yearsDischarged from PAH, RBWH, or TUH for an index diagnosis of AMI, or discharged from PAH or TUH for a CS admissionWilling and able to provide informed consent

The exclusion criteria are as follows:

Patients who are palliative or receiving end-of-life carePatients undergoing chemotherapy, radiation therapy, or dialysisPatients transferred to nonstudy hospitalsPatients who discharged against medical advicePatients who died during their admissionPatients admitted with type 2 myocardial infarctionPatients who reside outside of QueenslandPrevious RECARD patients returning with a new AMI or CS event

The intervention period will require prospective collection of data for patients in the intervention group, who will be consented before receiving the TOC service. Patients who receive usual care have a waiver of consent to collect inpatient data and readmission data (Figure 2).

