### Usual Care

Usual care across the hospital sites includes nurse and pharmacist involvement during admission and at discharge (as resources permit), according to standard operating procedures. All patients who are not identified as being at high risk of readmission during the intervention period, along with all patients in the prestudy period (usual care control group), will receive usual care and will not be provided the interdisciplinary pharmacist-led TOC service. Usual care typically does not include dedicated pharmacy support as part of postdischarge follow-up.

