### Statistical Analysis

An intention-to-treat analysis will be conducted. Participants who are lost to follow-up (ie, participants who do not complete the intervention, withdraw consent, or die during the study) will be included in the intention-to-treat analysis for the primary outcome. Participant characteristics will be summarized according to the prestudy and poststudy cohorts. Characteristics will be summarized and presented descriptively using mean (SD), median (IQR), and n (%), as required. Independent *t* tests and chi-square tests will be undertaken to determine whether there are any differences in baseline characteristics between the prestudy and intervention cohorts.

The primary outcome is a comparison of 30-day medication-related hospital readmissions in the prestudy cohort compared with the poststudy cohort. Secondary outcomes will be compared similarly. The analysis will consist of multivariable logistic regression. The explanatory variables will consist of a variable indicating the study period along with any relevant potential confounding variables we wish to control for (eg, patient age, sex, etc). The results for these outcomes will be considered significant at the 5% level, with 95% CIs reported. Subgroup analysis will also be undertaken to assess whether the clinical impact of the intervention varied by location (regional vs metropolitan sites), Indigenous and non-Indigenous patients, and high-risk patients identified according to the model of treating team referral.

Evaluation will be conducted using the RE-AIM framework as described earlier [20]. Data will be analyzed descriptively, and other metrics (eg, primary outcome) will be mapped as calculated above or informed by the patient survey and economic analysis.

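### The protocol contradicts itself on whether flagged high-risk patients who decline or cannot consent stay in the postcohort; excluding them could lower the post rate with no service effect

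*Protocol article*

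**What the plan says.** **Who is asked for consent.** Under Precohort: "A waiver of consent has been granted to collect these retrospective data for the historical usual care control group". Under Eligibility Criteria: "Patients who receive usual care have a waiver of consent to collect inpatient data and readmission data". The same section and Informed Consent require consent before the service is given. So only postcohort patients offered the service can refuse.

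**Text pointing to exclusion of decliners**
- Eligibility Criteria lists being willing and able to consent as an inclusion criterion, without limiting it to the service.
- Usual Care defines its recipients as "All patients who are not identified as being at high risk of readmission during the intervention period, along with all patients in the prestudy period". A flagged patient who declines is not in that description and is not in the intervention group either.
- Sample Size budgets for refusal: "We assume a minimal dropout and refusal rate of 10%; taking this into account, we aim to recruit 2211 participants into each 12-month period".

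**Text pointing to retention**
- Postcohort takes in all patients admitted with an index AMI or for CS in the period.
- The waiver in Eligibility Criteria, and the Public Health Act cover in Informed Consent, attach to patients who receive usual care. A decliner would in fact receive it.
- Secondary Objective plans a subanalysis of high-risk patients with and without the service.
- Statistical Analysis compares the two periods and states: "An intention-to-treat analysis will be conducted". Non-completers, withdrawals and deaths stay in.

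**Treated count.** Sample Size takes the top 25% by model and a further 10% by referral, then says: "We expect 35% of patients (~775 patients) to be flagged as high risk, consent to the study, and be given the TOC intervention".

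**The concern.** The primary comparison sets the whole precohort against the whole postcohort. Sample Size itself expects flagged patients to have a rate above 7%. If flagged patients who decline or cannot consent leave the postcohort, while comparable patients stay in the precohort under the waiver, the post side loses higher-risk patients and the pre side does not. The post rate then drops even if the service does nothing, in the direction that favours the service. No passage settles which rule applies.

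Three planning inputs also sit badly together:
- A refusal allowance is applied to a precohort in which nobody can refuse.
- A dropout allowance is applied although dropouts remain in the primary analysis.
- The same 35% is counted as flagged and as consenting and treated, which implies no refusal among the only patients who are asked.

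**Working it through.** **1. The plan's own figures.** Inputs: "Assuming a baseline risk of readmission of 7% and a significance level of .05" and "to detect an absolute risk difference of 2.1% with a power of 0.80", so 7% against 4.9%. The test's sidedness is not stated; two-sided 0.05 reproduces the figure. The two-proportion formula with pooled variance and no continuity correction gives 1991 per period (1988 with unpooled variance). Power at 1990 per period is 0.800, and 1990 / 0.9 = 2211.1. The arithmetic is sound.

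**2. Flagged and treated counts.** 25% + 10% = 35%, and 0.35 × 2211 = 774 (the stated ~775). If 10% of those decline, 77 are untreated and 774 − 77 = 697 are treated, which is 31.5% of 2211.

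**3. Spurious fall if decliners are excluded and the service has no effect.** The protocol gives no rate for flagged patients and no separate refusal rate, so these are assumptions:
- the overall rate is 7%, and flagged patients are 35% of the cohort;
- flagged patients carry a share s of events, with s = 0.5, 0.6 or 0.7, so the flagged rate is r = s × 0.07 / 0.35 = 10%, 12% or 14%;
- the R decliners removed have the average flagged rate.

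Post rate = (2211 × 0.07 − R × r) / (2211 − R).

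Example with R = 77 and r = 10%: (154.77 − 7.70) / 2134 = 6.89%, a fall of 0.11 points.

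The false-benefit chance is the probability that the two-sided 0.05 pooled z test is significant in the service's favour, with 2211 pre and 2211 − R post patients. Without bias it is 2.5%.

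| Decliners removed | Flagged rate | Post rate | Spurious fall (points) | Share of 2.1 | False-benefit chance |
|---|---|---|---|---|---|
| 77 (10% of flagged) | 10% | 6.89% | 0.11 | 5% | 3.4% |
| 77 | 12% | 6.82% | 0.18 | 9% | 4.2% |
| 77 | 14% | 6.75% | 0.25 | 12% | 5.1% |
| 221 (whole allowance) | 10% | 6.67% | 0.33 | 16% | 6% |
| 221 | 12% | 6.44% | 0.56 | 26% | 11% |
| 221 | 14% | 6.22% | 0.78 | 37% | 17% |

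The 221 rows are an upper bound. They need 221 / 774 = 29% of flagged patients to refuse, leaving 553 treated, which does not fit the protocol's own ~775.

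**4. If decliners are retained.** R = 0, the post rate under no effect is 7.00%, and this bias is zero.

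**5. Price of retention.** If the 2.1 points assumes that every flagged patient is treated, 10% untreated gives 2.1 × 0.9 = 1.89 points. Power at 2211 per period is then about 0.75; at the full 2.1 points it would be 0.84.

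**The case against.** The strongest reply is that exclusion is only inferred. A reader might take the consent criterion and the refusal allowance to mean that decliners are removed, and so that the post rate will fall and intention-to-treat fails. The documents do not support that as a statement of fact. The Postcohort definition, the waiver for patients who receive usual care, the subanalysis of high-risk patients without the service and the comparison by period all point to retention. Read literally, the consent criterion would also cover precohort and unflagged patients, who are never asked, and the text after the criteria ties consent to receiving the service. This stands, and it makes the bias conditional.

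It also stands that the 10% mixes dropout with refusal and is applied to both periods, so it is not a count of flagged refusers. An unneeded margin in a recruitment target biases nothing. The size depends on decliners' risk: at 75% of the average flagged risk, 77 exclusions give only 0.02 to 0.13 points, and at 7% risk there is no bias.

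Adjustment may help. Statistical Analysis allows any relevant confounder, and comorbidities, medications and laboratory results are to be collected in both periods. But the covariates are named only as examples, and part of the flagging is by clinician referral, so adjustment cannot be relied on to remove the bias.

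The treated count is a planning estimate that a local audit may change, and it does not enter the 1990. Finally, an article may leave details of analysis sets to the full protocol or SAP, which are not shown. That excuses silence; here the article's own eligibility, usual-care and sample-size statements pull against its cohort definition.

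**Conclusion.** The point holds as an unresolved contradiction about who is in the postcohort, not as a demonstrated bias. One reading is unbiased. The other removes flagged patients from the post side only and, if their risk exceeds 7%, favours the service. With 10% refusal among flagged patients and the assumptions above, the effect is modest: about 0.11 to 0.25 points, with a false-benefit chance of about 3.4% to 5.1% against 2.5%. The 0.33 to 0.78 points and 6% to 17% are an upper bound and should not be quoted as the expected size. The sample-size arithmetic is correct; the faults there are an allowance without a clear basis for the primary outcome and a treated count that leaves no room for refusal. The rule should be set now: Results reports recruitment continuing to November 2026 and no preliminary analysis.

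**What to change.** 1. In Eligibility Criteria, make willingness and ability to consent a condition for receiving the service, not for cohort membership.
2. In Usual Care and Statistical Analysis, state that every otherwise eligible flagged patient in the post period stays in the postcohort for the primary analysis, whether they accept, decline or cannot consent. Follow those not treated under the existing usual-care waiver and Public Health Act approval, after confirming with the ethics committee that these cover decliners.
3. In Sample Size, restate expected service recipients net of refusal (about 697, or 31.5% of 2211, at an assumed 10% refusal of flagged patients), and drop or justify the dropout and refusal allowance for the primary outcome.

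**Cost.** Wording, and possibly a minor amendment to confirm the waiver's scope; no extra patients or procedures. Retaining untreated decliners dilutes the average effect. The protocol should say whether the 2.1 points already allows for this and, if not, state the power of about 0.75 for 1.89 points at 2211 per period.

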### Statistical Analysis

An intention-to-treat analysis will be conducted. Participants who are lost to follow-up (ie, participants who do not complete the intervention, withdraw consent, or die during the study) will be included in the intention-to-treat analysis for the primary outcome. Participant characteristics will be summarized according to the prestudy and poststudy cohorts. Characteristics will be summarized and presented descriptively using mean (SD), median (IQR), and n (%), as required. Independent *t* tests and chi-square tests will be undertaken to determine whether there are any differences in baseline characteristics between the prestudy and intervention cohorts.

The primary outcome is a comparison of 30-day medication-related hospital readmissions in the prestudy cohort compared with the poststudy cohort. Secondary outcomes will be compared similarly. The analysis will consist of multivariable logistic regression. The explanatory variables will consist of a variable indicating the study period along with any relevant potential confounding variables we wish to control for (eg, patient age, sex, etc). The results for these outcomes will be considered significant at the 5% level, with 95% CIs reported. Subgroup analysis will also be undertaken to assess whether the clinical impact of the intervention varied by location (regional vs metropolitan sites), Indigenous and non-Indigenous patients, and high-risk patients identified according to the model of treating team referral.

Evaluation will be conducted using the RE-AIM framework as described earlier [20]. Data will be analyzed descriptively, and other metrics (eg, primary outcome) will be mapped as calculated above or informed by the patient survey and economic analysis.

